### **Sample size**

A total of 140 patients (randomised 1:1 to prednisolone or ciclosporin) will give the study at least 80% power at a 5% level of significance using a two-sided two-sample *t* test to detect a difference in means of 0.5 SDs of the primary outcome of velocity of healing at 6 weeks. The velocity of healing at 6 weeks is defined as the percentage change in surface area (measured by planimetry using digital photographs) over baseline of the target lesion. This sample size allows for an approximate 10% loss to follow-up at 6 weeks. These calculations were performed using Nquery 6.0.2 on Windows XP (Microsoft, Redmond, WA, USA).

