Differences between treatment groups for the primary and secondary outcomes will be assessed using Student’s *t* test. Linear regression models, adjusting for baseline covariates, will be used to compare the treatment groups at 6 weeks for the primary outcome, and any other continuous secondary outcomes that fit the assumptions. Cox regression models, adjusting for baseline covariates, will be used to compare the treatment groups in the analysis of the time to healing of the target lesion and the time to recurrence. Proportional odds models, adjusting for baseline covariates, will be used to analyse the categorical secondary outcomes, including global assessment of improvement and the inflammation assessment scale. The self-reported pain and the EQ-5D score will be summarised by the area under the curve (AUC), using Generalized linear models with the appropriate distribution. Patients are required to have the data recorded at the initial timepoint, and at the 6 week timepoint (for the 6 week analyses) or the final visit (for the final visit analyses), so only patients with at least the first observation and the last observation for the self-reported pain data, or those with both timepoints for the EQ-5D data, will be analysed in the first instance. Sensitivity analyses will be carried out for the self-reported pain outcome using the ‘last value carried forward’ method for patients who have missing interim data.

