### **Cost effectiveness**

Costs of the compared treatments will be assessed from the perspective of the health service, using resources such as inpatient stays, outpatient attendances, primary care appointments (at surgery), home visits by GP, district nurse visits and PG-related treatment costs. Cost effectiveness will be presented as the cost per healed ulcer at 6 months.

Health related quality of life will be estimated from responses to the Dermatology Life Quality Index. Quality-adjusted life years will be assessed from responses to the EQ-5D questionnaire, and the incremental cost per quality-adjusted life years gained will be presented for the compared treatments. Health state utilities will be calculated using UK population tariffs. Estimates of resource use (from medical records and patient diaries) will be combined with unit costs, to derive total costs. Unit costs will be based on study specific estimates and data from standard sources. Point estimates of mean incremental costs, QALYs, cost per QALY and cost per resolved episode at 6 months will be reported.

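### The EQ-5D area-under-the-curve model names no baseline adjustment, although the AUC itself includes baseline EQ-5D, so precision is lost and chance imbalance carries through

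*Protocol article*

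**What the plan says.** The Statistical analysis section of the protocol article goes through the regression models one family at a time. For the primary outcome, and for other continuous secondary outcomes that meet the assumptions: "Linear regression models, adjusting for baseline covariates, will be used to compare the treatment groups at 6 weeks for the primary outcome". Cox models for healing and recurrence are adjusted in the same way. For ordered outcomes: "Proportional odds models, adjusting for baseline covariates, will be used to analyse the categorical secondary outcomes". The next sentence turns to self-reported pain and the EQ-5D, which are to be "summarised by the area under the curve (AUC), using Generalized linear models with the appropriate distribution". It names no covariates. The section also lists Student's t tests for primary and secondary outcomes.

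To enter the AUC analysis a participant needs the initial observation and the 6-week one (or the final-visit one). The EQ-5D rule refers to having both timepoints. Under Secondary outcomes, EQ-5D is collected at baseline, 6 weeks and 6 months or healing. Pain is a daily diary over the first 6 weeks.

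The Cost effectiveness section adds: "Quality-adjusted life years will be assessed from responses to the EQ-5D questionnaire". It promises point estimates of incremental QALYs and cost per QALY, and does not describe how the QALY difference will be estimated.

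**The concern.** An EQ-5D AUC that begins at baseline contains a value that treatment cannot have changed. If the model does not condition on that value, a chance difference between the arms at baseline goes straight into the estimated treatment effect. It goes in again through the correlation between baseline and follow-up. The between-person variation in baseline also stays in the error term.

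Of the four regression families, this is the only one without an adjustment clause. A two-point EQ-5D AUC is also an outcome for which adjustment pays especially well. The same EQ-5D responses feed the QALYs. The Design section gives the higher cost of ciclosporin as a reason for a superiority trial, so a noisy QALY contrast would weaken a comparison that matters to the trial's purpose.

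**Working it through.** **The plan's own figure.** The article gives a sample size for the primary outcome only. It rests on a standardised difference of 0.5 between the arms, a t test, 80% power and a two-sided 5% level. By the normal approximation, n per arm = 2(1.96 + 0.8416)² / 0.5² = 62.8, so 63 per arm and 126 in total. Allowing for 10% loss, 126/0.90 = 140, as stated. The exact t test needs 64 per arm: 128/0.90 = 142.2, so 143, which is close. I use 63 per arm below. The article gives no figure for the AUC analyses.

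**Set-up.** Let w be the trapezoidal weights, scaled to sum to 1, and ρ a common correlation between assessments with equal variances (SD 1). The article gives neither the correlation nor the variances, so ρ = 0.3, 0.5 and 0.7 are assumptions. With R the correlation matrix, v = w′Rw is the unadjusted variance and c is the covariance of the AUC with baseline. Adjusting for baseline leaves v − c².

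**Baseline and week 6.** Weights are (1/2, 1/2), so v = c = (1 + ρ)/2 and the variance ratio is (v − c²)/v = (1 − ρ)/2.

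**Weeks 0, 6 and 26.** The intervals are 6 and 20 weeks, so the weights are (3, 13, 10)/26 and baseline has 3/26 = 11.5%. Here v = 0.411 + 0.589ρ and c = 0.115 + 0.885ρ. At ρ = 0.5, v = 0.706, c = 0.558, v − c² = 0.395 and the ratio is 0.56.

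| ρ (assumed) | 6 weeks: variance ratio | 6 weeks: SE multiplier | 26 weeks: variance ratio | 26 weeks: SE multiplier |
|---|---|---|---|---|
| 0.3 | 0.35 | 0.59 | 0.75 | 0.87 |
| 0.5 | 0.25 | 0.50 | 0.56 | 0.75 |
| 0.7 | 0.15 | 0.39 | 0.35 | 0.59 |

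The 26-week columns assume that the last assessment is at week 26. If healing brings it forward to week T (T of at least 6), baseline has weight 3/T, which lies between 11.5% and 50%.

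**Chance imbalance.** With 63 per arm, the baseline difference has SD √(2/63) = 0.178, so a 95% range of ±0.35 SD. In the 6-week AUC, an imbalance of 1 SD moves the unadjusted contrast by (1 + ρ)/2, that is 0.65, 0.75 or 0.85 SD. At ρ = 0.5, an imbalance of 0.35 SD moves it by 0.35 × 0.75 = 0.26 SD. A true week-6 difference of 0.5 SD (illustrative) shifts the AUC by only 0.5 × 0.5 = 0.25 SD.

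**Power.** For that illustrative effect with 63 per arm, power is 41%, 37% and 33% unadjusted and 84%, 90% and 98% adjusted, at ρ = 0.3, 0.5 and 0.7.

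**Simulation.** In 20,000 simulated trials at ρ = 0.5, both estimates averaged 0.25. The SE was 0.154 unadjusted and 0.078 adjusted.

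**Pain.** With about 42 daily entries, the first has weight 0.5/41 = 1.2%, and the article does not say that it is made before treatment. Under a constant correlation of 0.3 to 0.7, adjusting for it would leave 70% to 30% of the variance. That gain comes from correlation, not from the AUC containing the entry.

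**The case against.** The strongest reply is that the sentence is silent rather than wrong. The article presents itself as a summary of a fuller protocol, and covariate lists for secondary models often sit elsewhere. The clause on other continuous secondary outcomes might also reach the AUC, since a linear model is one kind of generalised linear model. This has some force: nothing in the article rules adjustment out, and a reader who infers a decision to omit it goes beyond the text. But the AUC has its own sentence with its own model, adjustment is stated for the three other families, and none of those statements says that the outcome's own baseline value is a covariate. Run as written, the model would be markedly less precise.

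Other stronger readings are tempting and do not hold:

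- **Pain.** The argument that the AUC contains the baseline value does not carry over. The first diary entry is not stated to precede treatment and weighs about 1.2%. If it follows the first dose, adjusting for it could remove part of the treatment effect.
- **Bias.** The unadjusted estimate is unbiased over randomisation. The harm is imbalance in the realised trial and lost precision.
- **The only unadjusted analysis.** This is true only of the regression families, because t tests are also listed.
- **An unadjusted QALY regression.** The article describes no QALY regression at all.

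It is also fair to say that the 50% weight belongs to the 6-week analysis. Over 6 months it is nearer 11.5%.

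**Conclusion.** The point stands for EQ-5D, as an avoidable loss of efficiency in a secondary outcome. The model as written names no baseline adjustment for an AUC in which baseline has half the weight at 6 weeks and about 11.5% over 26 weeks. Under equal variances and ρ between 0.3 and 0.7, adjustment would cut the standard error to about 59% to 39% of its unadjusted value at 6 weeks, and to 87% to 59% over 26 weeks. The weights follow from the assessment schedule, taking 6 months as 26 weeks. The standard-error figures rest on the assumed correlations and variances. For pain, only the general case for covariate adjustment remains. The primary analysis and the sample size of 140 are not affected.

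**What to change.** In the EQ-5D AUC model, name baseline EQ-5D and the two stratification factors (lesion size, and presence of underlying systemic disease) as covariates. Repeating the general phrase about baseline covariates would not be enough, because it need not include the outcome's own baseline. State that the incremental QALY difference will be estimated with the same baseline adjustment.

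For the pain AUC, adjust for the stratification factors. Add the first diary score only if it is recorded before treatment starts, and say which is the case.

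The cost is a change of wording. Baseline EQ-5D is already required of everyone in this analysis, and the stratification factors are recorded at randomisation. No participants are lost and no new data are needed.

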### **Cost effectiveness**

Costs of the compared treatments will be assessed from the perspective of the health service, using resources such as inpatient stays, outpatient attendances, primary care appointments (at surgery), home visits by GP, district nurse visits and PG-related treatment costs. Cost effectiveness will be presented as the cost per healed ulcer at 6 months.

Health related quality of life will be estimated from responses to the Dermatology Life Quality Index. Quality-adjusted life years will be assessed from responses to the EQ-5D questionnaire, and the incremental cost per quality-adjusted life years gained will be presented for the compared treatments. Health state utilities will be calculated using UK population tariffs. Estimates of resource use (from medical records and patient diaries) will be combined with unit costs, to derive total costs. Unit costs will be based on study specific estimates and data from standard sources. Point estimates of mean incremental costs, QALYs, cost per QALY and cost per resolved episode at 6 months will be reported.

### **Study organisation and funding**

The study is being coordinated through the UK Dermatology Clinical Trials Network [17] and the Nottingham Clinical Trials Unit at the University of Nottingham. It is funded by the National Institute for Health Research (NIHR) as part of an NIHR Programme Grant (RP-PG-0407-10177), and sponsored by the Nottingham University Hospitals NHS Trust. Further research nurse support is provided through the NIHR Clinical Research Networks [18].

The trial is being overseen by a Trial Steering Committee, which includes an independent chair and three other independent members (one of whom is a patient with PG). The DMC meets annually (or more frequently as required), and oversee all ethical and safety issues in accordance with current regulations and MRC guidelines for data monitoring committees. All members are independent of the study team, although the Trial Manager and some other members of the Trial Management Group (TMG) attend the open sessions in order to inform the DMC of trial progress. This committee meet at least once a year.

## **Discussion**

The STOP GAP trial is a unique study that could not be achieved without the collaborative efforts of large numbers of participating dermatologists, nurses, NHS Trusts and research networks. Recruitment is taking place at approximately 50 UK (and Ireland) secondary care dermatology departments, all of whom are contributing just 1 or 2 participants per year. Investigators are contributing on a voluntary basis because they believe that this is an important clinical question that will help to inform their clinical practice. Such a recruitment model means that it is not possible to provide dedicated STOP GAP research nurses at individual sites, and that the recruiting dermatologists are sometimes isolated. However, the development of the National Institute for Health Research (NIHR) Clinical Research infrastructure in the England (and CRC Cymru in Wales) means that support is now available to deliver collaborative trials of this kind, and many nurses are available within participating NHS Trusts to assist with patient recruitment and follow-up.

As a model for conducting trials of rare skin conditions, the STOP GAP trial is methodologically interesting in that efforts have been made to include all PG patients who are willing to take part, by inclusion in either the RCT or the observational study. This means that the trial will not only deliver the largest RCT ever to have been conducted in PG patients, but also the largest prospective case series of patients treated with topical therapy.

The use of a parallel observational study alongside the RCT also has advantages for recruitment as it means that patients with mild disease, who are initially considered to be ineligible for the main RCT, remain in contact with the trial team. If topical treatment fails and systemic therapy is indicated, these patients can then be considered for inclusion in the RCT. This approach is particularly useful for rare conditions, where few patients are seen at recruiting centres and the evidence- base for treatment is poor (making a prospective case series more valuable).

### **Trial status**

Recruitment into this trial started in May 2009 and is taking place in approximately 50 secondary care hospitals in the UK and Ireland. It is anticipated that recruitment will be completed by December 2012 at the latest.
